#### Intervention in the CG

The control participants will receive physiotherapy care based on the recent clinical practice guidelines from three different western countries: (1) American College of Physicians, USA (2017),^23^ (2) National Institute for Health and Care Excellence, UK (2016)^49 51^ and (3) Toward Optimized Practice, Canada (2015).^50^ These guidelines are used because they are recent and highly regarded. We did not find any evidence-based clinical practice guidelines for the management of LBP in Nepal or other developing countries. The CG interventions were derived by comparing the recommendations made by each of the three guidelines on specific management strategies. The CG treatment components were selected if: (1) two or more guidelines recommended the treatment component, (2) all the authors of the current study agreed that the component should be included, (3) the component was culturally acceptable and feasible to deliver in Nepal, (4) the component was determined to be appropriate to deliver at first contact and (5) the total duration of all of the components would sum up to 1 hour (approximately) to make the contact hour comparable with the approximately 1 hour of pain education that would be provided to the experimental group. Similarities and differences in the clinical practice guidelines across the countries are common and are influenced highly from the experience of the expert committee responsible for developing a clinical practice guideline and local practice trends.^52^ For this reason, we chose to adapt the recommendations made in the available guidelines to fit with the expertise of the local physiotherapist, practice trends that are widely accepted in Nepal and the feasibility of delivering the treatment within the context of the study.

Thus, the CG intervention will contain of: (1) education (advice to remain active, education about prognosis of LBP for acute LBP and avoid bed rest and braces)^23 50 51^ for 10–15 min, including time spent to listen to each participant’s pain story; (2) back massage^23 51^ for about 10 min; (3) superficial heat^23 50^ for 10–15 min; and (4) static cycling or (treadmill) walking with the aim to promote physical activity^23 50 51^ including any rest period for a total of approximately 20 min. Although superficial heat is recommended in the acute/subacute LBP,^23 50^ we included this as a common treatment for all types of LBP including chronic LBP, which could be a part of self-management. Any forms of electrotherapy and acupuncture will not be offered to the study participants.^49^ The control intervention will strictly exclude the use of pain biology education.

#### Dosage of intervention for the CG

The control intervention will last for 1 hour to match the experimental group.

#### Home advice for the CG

Participants will be advised to self-manage their back pain based on the information provided. Home exercise leaflet with emphasis on the value of exercise to increase strength and endurance, followed by a 30 min walking. Advice preceding the exercises will state that exercises are needed to keep you strong, healthy and pain free. A written instruction to perform general exercises and physical activity will be sent to the participants. Participants will be discouraged to use a lumbar corset and rest as coping strategy, and return to work and physical activity will be encouraged in the control participants, as they are in the experimental group. A reminder to perform home exercises will be sent to all the participants for 5 days during the week.

### Outcome measures

The details of primary feasibility outcomes are presented in table 2.

**Table 2 T2:** How will each primary feasibility objective be assessed?

Serial Number	Objectives	Measures to assess specific objectives	Statistical analysis
1	Willingness to participate in a randomised controlled trial	All the consecutive participants presenting at the physiotherapy department will be approached and invited to participate. The number and rate of participants willing versus not willing to participate will be recorded, as well the reasons for not wanting to participate.	Total number of patients not willing to participate will be summed and reasons for non-participation collated.
2	Feasibility of blinding the assessor	Feasibility of blinding will be assessed by asking the assessor two questions at the end of the follow-up assessment: 1. Did you receive any information that indicated to you which group the participant was assigned to? 2. How did you receive information about group assignment? Assessor’s guess regarding group assignment group will be recorded for each participant. The responses will be coded as correct or incorrect guess.	The frequency and relative rates of ‘*Yes*’ and ‘*No*’ as the answer to the first question will be computed, as will the frequency and relative rates of correct and incorrect guesses. Finally, reasons for guesses will be recorded as verbatim and reported.
3	Eligibility and recruitment rates	The total number of participants screened, found eligible and recruited will be recorded during the screening and recruitment process. The reasons why the participants were ineligible for study inclusion will be recorded for every participant who did not meet eligibility criteria. Reasons for declining participation will be recorded for every eligible individual who declined participation. Consent rates will also be recorded.	The number of participants screened, who were eligible, who consented to participate, who refused to participate will be computed. The reasons for exclusion and refusal will also be collated.
4	Acceptability of screening procedures	The lead researcher will interview the physiotherapist(s) screening the potential participants for eligibility by asking the following open-ended question at the end of every week, ‘*Were there any difficulties or challenges in screening and recruiting the participants the past week?*’ The responses will be recorded as ‘Yes’ or ‘No’. If the answer to this question is ‘Yes’, the lead researcher will ask the following open-ended question, ‘*What were the difficulties and challenges?*’. Responses will be written down verbatim. Additionally, the outcome assessor will complete a form every time he or she encounters a difficulty or a challenge during screening. Outcome assessors will also be asked about their recommendations for overcoming any challenges that they identify. Time taken to complete the questionnaires will be recorded.	The frequency of difficulties or challenges will be counted. The difficulties and challenges will be noted, categorised if possible, and reported. Results will be used to improve the screening procedure in the full trial in future, and therapists’ recommendations will be considered.
5	Acceptability of random allocation to a treatment group	Outcome assessor will ask the participants if random allocation to one of the two treatment groups is acceptable to the participants. Responses will be recorded as ‘Acceptable’, ‘Not acceptable’ or ‘No preference’.	The frequencies of each response will be computed separately for each treatment condition.
6	Understanding possible contamination between the groups	Contamination between the groups will be assessed by asking all the study participants the following questions at 1 week following treatment: *1. ‘Have you talked to other participants in this study about the intervention they are receiving?’; If yes, further ask, ‘Was your attitude towards the intervention, or intervention changed after talking to one of the participants in the other group?’;* *2. ‘Are you aware of the intervention that any participants in the other group are receiving in the study?’;* *3. Are any of the participants in the other group aware of the type of intervention you are receiving in this study?’* Participants in the control group will be asked the following question: ‘*Did you read the pain education booklet or watch the video which is one of the components of the intervention group*?’ These questions are adapted from a cotwin controlled feasibility trial.^62^	The frequencies of the participants who responded affirmatively to each question will be computed separately for each treatment condition.
7	Credibility and acceptability of the interventions	Treatment credibility will be assessed using five questions adapted from Borkovec and Nau.^63^ The questions will be modified to fit ‘Pain education’ and ‘Control group’ as a treatment for patients with LBP and will be administered to all the participants in both conditions. One, important cultural adaptation for the scoring will be made by changing the numerical scale proposed by Borkovec and Nau to a Verbal Rating Scale, because Numerical Rating Scales have been shown to be unsuitable in Nepalese with musculoskeletal pain, especially in those who are older and have low educational attainment.^64^ Responses for each of the five questions will be recorded on a Likert scale where, 0=‘*Not at all*’, 1=‘*A little bit*’, 2=‘*Somewhat*’, 3=‘*Quite a bit*’, 4=‘*Very much*’. The questions are: 1. How logical does the treatment provided seem to you for the management of low back pain? 2. How confident would you be that this treatment would be successful in reducing pain? 3. How confident would you be in recommending this treatment to a friend or family who also has LBP? 4. If you were having low back pain again, would you be willing to undergo such treatment? 5. How successful do you feel this treatment would be in reducing pain in other parts of the body, for example, knee pain? All the questions will be asked at baseline and at 1 week following treatment.	Mean of the total scores on the credibility scale will be computed separately for each condition. Between-condition differences in creditability will be evaluated using a t-test.
8	Adherence to the intervention	Adherence to treatment will be assessed by asking the participants in both conditions to maintain a record of daily home treatment that was followed by every participant. The participants will tick mark a box for every day for a total of 5 days between the two assessment time-points to indicate their adherence to prescribed home exercise programme. Additionally, participants will be requested to record any deviation of prescribed home treatment programme (eg, additional visit to the clinic and use of other interventions). Finally, question regarding non-adherence will be asked.	The total number of treatment adherence days will be summed for each treatment condition separately. Deviation from the treatment protocol will be recorded. Finally, the reasons for non-adherence will also be listed.
9	Satisfaction of treatment	All the participants in both the conditions will be asked to respond to the Patient Global Assessment of Treatment Satisfaction scale at 1 week following treatment.^65 66^ The question asked will be, ‘*How satisfied are you overall with the study treatment?*’ Responses to this question are made on a five-point categorical scale (0=‘*Very dissatisfied*’; 1=‘*Dissatisfied*’; 2=‘*Neutral or no preference’*; 3= ‘*Satisfied*’; 4=‘*Very satisfied*’).	Mean treatment satisfaction scores will be computed for each treatment condition separately. Between-condition differences will be evaluated using a t-test.
10	Difficulty in understanding the information provided by the physiotherapist.	All the participants will be asked about the difficulty in understanding the information provided by the physiotherapist. The question asked will be, ‘*How difficult was it for you to understand* the *information provided by the physiotherapist?*’ Responses will be provided on a 5-point Likert scale, where 1=‘*Very easy*’, 2=‘*Easy*’, 3=‘*Neither easy nor difficult*’, 4=‘*Difficult*’, 5=‘*Very difficult*’.	The differences in the difficulty in understanding the information provided will be compared between the two groups.
11	Difficulty in understanding the instructions for what to do.	All participants will be asked about the difficulty in understanding the instructions provided by the physiotherapist for what to do at home. The question asked will be, ‘*How difficult was it for you to understand the instructions provided by the physiotherapist for what to do at home?*’ using a on a 5-point Likert scale, where 1=‘Very easy’, 2=‘*Easy*’, 3=‘*Neither easy nor difficult*’, 4=‘*Difficult*’, 5=‘*Very difficult*’.	Frequencies and rates of each response category will be computed for each group separately.
12	Adverse events	All participants will be asked about any adverse events after treatment. All responses will be recorded verbatim.	The number of adverse events listed will be computed for each treatment condition separately. The responses will be analysed qualitatively (see text).

LBP, low back pain.

All but one secondary outcome measures have been shown to be reliable and valid in Nepali populations. The measure of quality of life (QOL) is not yet validated at the time of writing the protocol; however, we have included it as a secondary outcome measure, because assessment of QOL is a recommended measure by core outcome sets in clinical trials for LBP.^53^ We hypothesise that this measure is comprehensible and will show adequate validity in the Nepalese sample. We will evaluate the validity of the measure before using it in the full clinical trial.

A research assistant will interview all the study participants to make the study procedures consistent and to allow for the inclusion of participants with little or no education. The interviews will be administered by a physiotherapist who will be blind to group assignment. Secondary measures include the four PROMIS short-form measures assessing pain interference,^54^ pain intensity,^54^ sleep disturbance,^54^ and depression,^54^ as well as the 13-item Pain Catastrophizing Scale,^55^ Connor-Davidson Resilience Scale,^56^ Global Rating of Change^57 58^ and a QOL scale. All the items in each PROMIS measure will be summed to obtain raw scores for each scale. The raw scores of each measure will then be converted to T-scores, with a mean of 50 and SD of 10 and recorded (www.assessmentcenter.net). Details of the measures with their measurement properties are presented in table 3.

**Table 3 T3:** Secondary outcome measures

Domain	Name of outcome measure	No. of Items	Response scale	Scoring	Measurement properties of Nepali versions of the scale
Pain interference	PROMIS Pain Interference short-form 6b^54^	6	5-point, ordinal	Respondents are asked to rate how much pain interfered with their daily life (eg, enjoyment of life, ability to concentrate and day-to-day activities) in past 7 days on 5-point Likert scales (=‘*Not at all*’, 2=‘*A little bit*’, 3=‘*Somewhat*’, 4=‘*Quite a bit*’, 5=‘*Very much*’). Responses are scored as a T-score that can range from 0 to 100, with a mean of 50 and SD of 10 in the normative sample.	Good internal consistency (Cronbach’s alpha=0.85). Excellent reliability (ICC=0.80) in a sample of individuals with chronic pain from Nepal.^54^
Pain catastrophising	Pain Catastrophizing Scale (PCS)^55^	13	5-point, ordinal	Respondents are asked to indicate the degree or frequency with which they have each catastrophising response listed when they ‘… are experiencing pain’ on a 5-point Likert scale (0=‘*Not at all*’, 1=‘*To a slight degree*’, 2=‘*To a moderate degree*’, 3=‘*To a great degree*’ and 4=‘*All the time*’). The total PCS score can range from 0 to 52, with higher scores representing higher pain catastrophising.	Good to excellent internal consistencies: Cronbach’s alpha=0.85–0.93. Excellent test–retest stability (ICC=0.89–0.90). Positive moderate correlations with measures of pain intensity, depression and anxiety in a sample of individuals with chronic pain from Nepal.^55^
Patient’s global rating of change	Global Rating of Change^57 66 67^	1	1–7, ordinal	Respondents are asked to rate their ‘*overall improvement*’ their health condition since the study enrolment. Responses can range from 1 to 7 with 4=‘*No change*’. Scores greater than 4 indicate greater improvement and scores lower than 4 indicate a perceived worsening in the respondent’s health condition.	MIC: 1 point change.^57 58^
Quality of life (QOL)	QOL rating scale	2	5-point, ordinal	Respondents are asked to rate their general QOL and general health by responding to the questions: •‘*In general, how would you rate your overall quality of life during the past week?*’ •‘*How would you rate your general health during the past week?*’ The response options are: 1=‘Very bad’, 2=‘Bad’, 3=‘Fair’, 4=‘Good’ and 5=‘Very good’.^68^ Greater score indicate better QOL.	Not available during the time of protocol writing the study protocol.
Pain intensity	PROMIS Pain Intensity short-form 3b^54^	3	5-point, ordinal	Respondents are asked to rate their current pain and their worst and average pain intensity in past 7 days on 5-point Likert scales (1=‘*Had no Pain*’, 2=‘*Mild*’, 3=‘*Moderate*’, 4=‘*Severe*’, and 5=‘*Very severe*’). Responses are scored as a T-score that can range from 0 to 100, with a mean of 50 and SD of 10 in the normative sample.	Good test–retest reliability (ICC=0.71) in a sample of individuals with chronic pain from Nepal.^54^
Sleep disturbance	PROMIS Sleep disturbance short-form 8b^54^	7*	5-point, ordinal	Respondents are asked to rate sleep quality items on a 5-point Likert scale. Responses are scored as a T-score that can range from 0 to 100, with a mean of 50 and SD of 10 in the normative sample.	Although the Nepali translation of the 8-item Sleep Disturbance short-form showed poor reliability, removal of one item, improved the test–retest stability to excellent. (ICC=0.78). Good internal consistency of 7-items (Cronbach’s alpha=0.89).^54^
Depression	PROMIS Emotional Distress- Depression short-form 8b^54^	8	5-point, ordinal	Respondents are asked to indicate the frequency of depressive symptoms in the past 7 days on a 5-point verbal rating scale (1=‘*Never*’, 2=‘*Rarely*’, 3=‘*Sometimes*’, 4=‘*Often*’ and 5=‘*Always*’). Responses are scored as a T-score that can range from 0 to 100, with a mean of 50 and SD of 10 in the normative sample.	Excellent internal consistency (Cronbach’s alpha=0.93). Excellent test–retest reliability (ICC=0.81) in a sample of individuals with chronic pain from Nepal.^54^
Resilience	10-item Connor Davidson Resilience Scale^56^	10	4-point, ordinal	Respondents are asked to rate each resilience item on a 5-point Likert scale: 0=‘*Not true at all*’, 1=‘*Rarely true*’, 2=‘*Sometimes true*’, 3=‘*Often true*’, and 4=‘*True nearly all the time*’. Responses are summed such that total scores range from 0 to 40, with higher scores indicating more resilience.	Good to excellent internal consistency (Cronbach’s alpha=0.87–0.90).^56^ Excellent test–retest stability (ICC=0.89).^56^ SE of measurement=2.42 points. Minimum detectable change=6.72 points. Significant negative and moderate association with the PCS in a sample of individuals with chronic pain from Nepal.^56^
Use of pain medications and other pain treatments	–	–	–	Names and dosage of pain medication intake will be recorded by the assessor by asking the research participant via interview. Medications will then be categorised into analgesic type (opioids, non-steroidal anti-inflammatory drugs, sedatives and antiseizure medications), as will the number of days each type of medication is taken. Other pain treatments provided to or used by the study participants will also be recorded and classified (eg, physical therapy and naturopathy). The number of days each treatment was provided to or used by the participants will be recorded.	No validity data for self-reported analgesic or pain treatment use in Nepali patients available at the time of protocol writing.

*Only seven items out of eight items will be included, as the measurement properties of the total eight-item was poor, and only after removal of one item, the reliability improved.

ICC, Intraclass Correlation Coefficient; MIC, minimum important change; SE, standard error.

The risk of adverse events in both the groups are very low. Participants will be asked to choose the amount of home exercises (such as walking) they will perform based on a level that is comfortable. Participants will be asked to change the duration and/or pace of exercises if they feel the initial level is too high.^59^ Participants will be asked to record any adverse events that occur and report these to the researcher. Adverse events in both the groups will be reported and compared between the groups.

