### Aims and objectives

The primary aim of the study is to evaluate the feasibility of a full randomised clinical trial (RCT) for assessing the effects of pain education as an intervention for patients with LBP of any duration in a physiotherapy facility in Nepal after developing culturally appropriate, evidence-based pain education materials. The primary objectives of the study are related to feasibility of an RCT, specifically: (1) willingness to participate in an RCT, (2) feasibility of assessor blinding, (3) eligibility and recruitment rates, (4) acceptability of screening procedures and random allocation, (5) possible contamination between the groups, (6) intervention credibility for patients with LBP, (7) intervention adherence, (8) treatment satisfaction and (9) difficulty in understanding the intervention being provided.

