### Overview of the study

Advertisement of the trial will be made in social media, and all the patients with LBP presenting at the study site will be invited to participate. Interested candidates will be screened for eligibility. Eligible patients with non-specific LBP will then be enrolled in the trial and be randomly assigned to one of the two study groups. All the participants in the experimental group will receive pain education and those in the control group (CG) will receive guideline-based physiotherapy treatment. All the participants will be assessed at baseline and 1 week following treatment. Details describing the schedule of enrolment, interventions and assessment are presented in table 1, in the manner recommended by SPIRIT checklist.^32^

**Table 1 T1:** Schedule of enrolment, assessment and interventions

Timepoint	Study period				
	Enrolment	Allocation	Post allocation		Final Assessment
	−T_1_	T_0_	T_1_	T_2_	T_3_
Enrolment					
Eligibility screening	X				
Explain study procedure/provide participant information sheets	X				
Informed consent	X				
Random treatment allocation		X			
Intervention					
Experimental intervention (PEG)				X	
Control group (CG)				X	
Assessment					
Baseline descriptive variables					
Sociodemographic information (age, sex, address, occupation, religion and ethnicity)			X		
History					
Pain history (site of pain, duration of pain, continuous or intermittent pain, aggravating and relieving factors)			X		
Comorbidities			X		
Feasibility					
Willingness to participate in a randomised controlled trial	X				
Acceptability of random allocation to one of the two groups	X				
Acceptability of intervention session (one session in a week with home treatment programme throughout the week)	X				
Feasibility of blinding the assessor*					X
Eligibility and recruitment rates	X				
Acceptability of screening procedures*					W
Understanding possible contamination between the groups					X
Evaluating the credibility of the intervention			X		X
Adherence to intervention					X
Treatment satisfaction					X
Difficulty in understanding the treatments					X
Secondary outcomes					
PROMIS Pain interference			X		X
PROMIS Pain intensity			X		X
Quality of life			X		X
PROMIS Sleep disturbance			X		X
PROMIS Depression			X		X
GROC			–		X
PCS			X		X
CD-RISC-10			X		X

*Assessed by the therapist providing intervention; all other outcomes are assessed by the blinded outcome assessor.

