### Participant screening and recruitment

Consecutive participants with non-specific LBP will be invited to participate in this study. The study purpose and procedures will be described to potential participants. This will include information about the benefits and potential harms of the intervention, the time required for the completion of the study, follow-up duration, voluntariness of participation, cost of participation and the rights to withdraw from the study at any point. A study information sheet will be provided to all potential participants.

If the potential participants are interested in participating, they will be screened for eligibility by a research assistant who is a physiotherapist. If the participants are found eligible, informed consent will be obtained. For those who cannot sign the consent, a witness will sign on their behalf, or the study participant will provide a thumb print on the form for those who cannot write or sign the form as per the ethical guidelines provided by Nepal Health Research Council (NHRC). We will include uneducated patients who cannot sign an informed consent in order to increase the inclusion of uneducated or low education group, given that 31% people in Nepal who are 5 years old or more cannot read and write.^37^ Additionally, exploration of feasibility of pain education in those with no schooling or low educational attainment is important in order to inform clinical practice.

Participants will be informed that they will receive one of the two treatments randomly. It will be highlighted that both of the treatment options are thought to be effective for LBP and that the goal of the main study is to compare the interventions; however, the current study will more specifically evaluate the feasibility of such a study.

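### Acceptability of random allocation is tabulated only for patients who agreed to be randomised, so the result is selected towards acceptance by an amount it cannot show

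*Protocol article*

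**What the plan says.** The Aims and objectives section lists, among the primary objectives, "4) acceptability of screening procedures and random allocation". Table 2 splits this into item 4 (screening) and item 5 (random allocation).

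For item 5 the measure is: "Outcome assessor will ask the participants if random allocation to one of the two treatment groups is acceptable to the participants". There are three answer options: "Responses will be recorded as ‘Acceptable’, ‘Not acceptable’ or ‘No preference". The analysis cell reads: "The frequencies of each response will be computed separately for each treatment condition". The Data analysis plan section refers to Table 2 for the analysis of the primary feasibility objectives, so this is the planned analysis of item 5.

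Three other places bear on it:
- Participant screening and recruitment: "Participants will be informed that they will receive one of the two treatments randomly".
- Table 1, in the Overview of the study, has a row "Acceptability of random allocation to one of the two groups". It is marked at enrolment, ahead of the allocation time point.
- Table 2 item 1: "The number and rate of participants willing versus not willing to participate will be recorded, as well the reasons for not wanting to participate". Item 3 likewise records why each eligible person who declined did so, and collates the reasons.

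**The concern.** The attitude being measured also affects who gets into the table. A patient for whom random assignment is decisive can learn of it during recruitment and decline. That patient then has no treatment condition and is absent from item 5. The people left are those for whom randomisation was at least tolerable enough to consent.

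A reader of the acceptability result for this primary objective would therefore see consenters' answers only. The Introduction says it is not known whether a full trial is feasible in this population. What a full trial needs to know is how patients who could be invited regard randomisation, and item 5 by itself does not tell it that.

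**Working it through.** **Step 1: who is in the denominator.** The Sample size section plans 20 patients per condition, so 20 + 20 = 40. A tabulation by treatment condition has at most these 40 people in it. The plan states no expected acceptability figure, so there is none to reproduce.

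**Step 2: what the split by arm can show.** Table 1 puts the question before allocation. Answers given then cannot be influenced by the arm, so any difference between arms is chance. The split adds little, and it is also what restricts the denominator.

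**Step 3: size of the selection.** Let
- a = true share of eligible patients who do not object to randomisation,
- c1 = probability that such a patient consents,
- c0 = probability that an objector consents.

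Tabulated share not objecting = a·c1 / [a·c1 + (1 − a)·c0].

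All three are assumptions, since the documents give none of them. With c1 = 0.8:

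| True a | c0 = 0 | c0 = 0.1 | c0 = 0.3 | c0 = 0.8 |
|---|---|---|---|---|
| 0.9 | 100% | 98.6% | 96.0% | 90% |
| 0.7 | 100% | 94.9% | 86.2% | 70% |
| 0.5 | 100% | 88.9% | 72.7% | 50% |
| 0.3 | 100% | 77.4% | 53.3% | 30% |

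Example: a = 0.5, c0 = 0.1 gives 0.40 / (0.40 + 0.05) = 0.889. The figure is biased upward whenever c0 < c1 and unbiased when c0 = c1. Item 5 contains nothing from which c0 could be estimated.

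**Step 4: the same in counts.** Take a = 0.7, c1 = 0.8, c0 = 0.1.
- Overall consent is 0.7 × 0.8 + 0.3 × 0.1 = 0.59, so 40 / 0.59, or about 68 eligible patients, are needed.
- Objectors: 0.3 × 68 = 20.4. About 2 enrol and 18 decline.
- Non-objectors: 47.6. About 38 enrol and 10 decline for other reasons.
- Item 5 as planned: 2/40 = 5% object.
- Among all eligible patients, with the 18 refusals counted: (18 + 2)/68 = 29.4%. If the 10 other decliners are all treated as objectors as well: 30/68 = 44.1%.

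**Step 5: sampling error does not cover the gap.** With no 'Not acceptable' answers, the exact two-sided 95% upper limit is 1 − 0.025^(1/n): 8.8% for n = 40 and 16.8% for n = 20 per arm. These limits apply to consenters only.

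**The case against.** The strongest reply is that the trial does collect the missing information. Item 1 covers all consecutive patients approached and gives the number, the rate and the reasons for those unwilling. Item 3 adds consent rates and reasons for every eligible decliner. Two sites with different levels of refusal would therefore differ visibly in those results. This stands, and it rules out the stronger reading that half of objective 4 goes unanswered. What it leaves is a gap in linkage: neither item names randomisation or treatment preference as a category, and neither feeds into the acceptability result.

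A reader might also infer that item 5 will come out near 100% whatever patients think. The documents do not support that. It holds only if almost all objectors decline, and no decline rate is given. Enrolled patients can still answer 'Not acceptable', and the table in the working shows values down to the true one.

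Nor do the documents support saying that the full trial would be planned on false reassurance. Table 4 has no criterion on acceptability of allocation. Its recruitment-rate criterion, when it fails, calls for the reasons behind low participation to be identified.

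It can also be said that Table 2 uses the word participants for people who were not enrolled, and that Table 1 places the question at enrolment, so decliners may in fact be asked. That is possible, because the text does not settle it. The analysis cell would still leave their answers out.

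Finally, the 'No preference' option is not a fault in itself. All three frequencies are reported, so nothing is lost.

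**Conclusion.** The point holds in a limited form. As written, the analysis of item 5 covers only patients who agreed to be randomised. It overstates acceptability among eligible patients if objectors consent less often than others, and it cannot show by how much. With 50% true acceptance and 80% consent among accepting patients, the tabulated figure lies anywhere from 100% to 50% as objectors' consent rises from 0 to 0.8. These inputs are assumptions chosen to show the range. They are not estimates for this site.

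That the denominator is restricted, and that a split by arm of answers given before allocation is uninformative, follows from the text without any assumption. The consequence is confined to how one component of a primary objective is reported. No progression decision in Table 4 depends on it, and the refusal data needed to repair it are already to be recorded.

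**What to change.** Change Table 2 item 5 as follows:
- Report the responses of all eligible patients to whom random allocation was explained at enrolment, overall and by consented versus declined.
- Add a code for randomisation or treatment preference to the refusal reasons already recorded under items 1 and 3.
- Report, with an exact 95% CI, the number and proportion of eligible patients who either refused for that reason or answered 'Not acceptable', counting each patient once.
- Show those who declined for other reasons, and those who gave none, as separate counts. Do not count them as accepting. Give the proportion under both extremes: none of them objects, and all of them object.
- Keep the table by arm as a secondary description.

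The cost is a wording change, one extra code in the refusal record, and one question put to decliners who are willing to answer it. The reported figure will probably be less favourable, and some decliners will give no reason, which widens the range between the two extremes. The sample size and the Table 4 criteria stay as they are.
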